### Recruitment and consent

Recruitment for the study takes place at the first consultation with a midwife at the obstetric ambulatory clinic, which is on average at 18 week’s gestation. Preliminary eligibility for the study is determined in a collaboration between the midwife and the pregnant woman based on her medical record, reason for referral to the ambulatory clinic and her present surplus of mental resources. The midwife will provide verbal information about the study, and email written information to eligible women, who express an interest in participating in the study. Name, contact information and reason for referral is then passed on to the responsible researcher, who will schedule an interview. The interview will take place either online or at the outpatient clinic. The online format provides the women with an opportunity to participate in the interview in their own homes. Our experience working with this population, led to offering this option. We offer the possibility of conducting the interview at the outpatient clinic if it is not possible online. The interview contains information about the study, eligibility criteria, procedures, randomization and the intervention. Inclusion criteria for the study are estimated due date no sooner than three months from start of the intervention, eighteen + years of age, able to speak and write Danish and written informed consent to study criteria. Exclusion criteria are an active substance dependence, psychotic disorders (e.g. schizophrenia or bipolar disorder), suicidality and being unavailable for two or more of the scheduled prenatal MBSR classes. Pregnant women who fulfill the eligibility criteria and consent to study participation must sign a consent form no later than one week from the interview. The responsible researcher (first author) obtains written informed consent.

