***Exploratory outcome measures***						
Maternal Antenatal Attachment Scale	Antenatal attachment	X		X		
The Childbirth Experience Questionnaire	Childbirth				X	

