***Mediators of outcome***						
The Five-Facet Mindfulness Questionnaire	Mindfulness	X	X	X	X	X
The Self-Compassion Scale	Self-compassion	X	X	X	X	X

T0 = Baseline; T1 = 1½ months post-randomization; T2 = 3 months post-randomization; T3 = 6 months post-randomization; T4 = 9 months post-randomization

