### Exploratory outcome measures

#### The Maternal Antenatal Attachment Scale

The Maternal Antenatal Attachment Scale (MAAS) is a widely used measure of the maternal-fetal bond [50]. The maternal-fetal bond has been defined as “the emotional tie or bond which normally develops between the pregnant woman and her unborn child” [51]. The theoretical basis of MAAS is a hierarchical model of adult attachment [50]. Within this model, the core experience of maternal attachment is the mothers love for her unborn child. The MAAS consists of 19 items covering two subscales: 1) Quality of attachment (11 items) and time spent in attachment mode (8 items) [52]. All items are rated on a five-point scale. The minimum score for the total MAAS is 19 and the maximum is 95. The scores for the subscales range between 11 and 50 (Quality of attachment) and between 8 and 40 (Time spent in attachment mode). Higher scores reflect, respectively, a positive quality of attachment and a high intensity of preoccupation with the fetus [52]. Moreover, MAAS scores can be divided into four maternal attachment styles based on mean scores on the two subscales [53]. The MAAS has demonstrated good psychometric properties in terms of structural validity and internal consistency [54].

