### Statistical analysis plan

Statistical analyses will be performed using SPSS for Windows (version 28; IBM Corp, Armonk, NY) or Stata (version 16). Recruitment, participation and retention rates will be reported in a CONSORT flow diagram [58]. Analyses on the primary outcome will be conducted on the intent-to-treat population meaning all randomized participants with completed baseline assessments. Compliance is considered as participation in five or more of intervention-scheduled classes.

Baseline sociodemographic data will be presented by means of frequencies (percentages), medians (interquartile range), and means (SD), according to their level of measurement and statistical distribution.

Statistical analysis of primary outcome, mental wellbeing, will be performed using a repeated measurement model with systematic effects, randomization arm, time (baseline, 3, 6 and 9 months post-randomization), intervention (prenatal MBSR, waitlist control group), interaction between time and intervention, baseline values of: age, perceived stress and use of psychotropic drugs. The model will include random effects of person and “scheduled group”. The primary effect estimate is the mean difference in change since baseline between the intervention group and the control group at nine months post-randomization. The change from baseline at 3 and 6 months will also be reported. Equivalent models will analyze secondary outcomes, stress, anxiety and depression. The change from baseline to three months after randomization in maternal antenatal attachment will be analyzed in a model with the systematic effect of intervention, baseline mental wellbeing, perceived stress, age, number of children and random effect of “scheduled group”. Equivalent models will be used in the analysis of experience of childbirth. A per-protocol analysis of the primary outcome will be performed with three intervention levels: (1) attending five or more of intervention-scheduled sessions, (2) attending less than five of intervention scheduled sessions and (3) waitlist control group. No subgroup analyses is planned. Standard errors will be based on the bootstrap method, resampling persons.

The five measurement points allow to test whether changes in the proposed mediators, i.e. mindfulness and self-compassion, are associated with changes in the proposed outcomes. Structural equation modelling will be used for the statistical analyses of the proposed mechanisms [59].

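### The only follow-up attachment form and the only childbirth form are timed from randomization, so for a few eligible women either can fall on the wrong side of the birth (minor; exploratory outcomes only)

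*Protocol article*

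**What the plan says.** All points are from the protocol article.

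- **Attachment.** Table 2 marks the MAAS at T0 and T2 only. Under Statistical analysis plan: "The change from baseline to three months after randomization in maternal antenatal attachment will be analyzed in a model with the systematic effect of intervention". The measure's own section defines what is scored as "the emotional tie or bond which normally develops between the pregnant woman and her unborn child".
- **Childbirth experience.** Table 2 marks the CEQ once, at T3, and its footnote gives "T3 = 6 months post-randomization". The analysis uses models equivalent to the attachment model, with baseline wellbeing, perceived stress, age and number of children as covariates. Time since birth is not among them.
- **Gestation at entry.** Under Recruitment and consent: "Inclusion criteria for the study are estimated due date no sooner than three months from start of the intervention". Table 1 puts the start of the intervention 2 weeks after randomization. No latest due date and no minimum gestation is stated. The first consultation is described as one "which is on average at 18 week’s gestation", which is an average without a range.
- **Reminders.** Under Outcomes, non-responders are emailed after one week.
- **Status.** Both measures are listed as exploratory and belong to the fourth study aim.

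**The concern.** The MAAS asks about an unborn child and the CEQ asks about a birth that has taken place. A clock running from randomization puts each form on its proper side of birth only if gestation at randomization is held within limits. The eligibility rule limits one end, with a narrow margin, and leaves the other end open.

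A MAAS answered after delivery does not measure the stated construct. A CEQ sent before delivery cannot be answered, and no later one is scheduled. Imputation does not help with the first case, because an antenatal attachment score has no clear meaning once the child is born. Even among women on the right side of birth, the interval from birth to the CEQ differs widely, which adds variation that the stated model does not absorb.

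At stake are the validity and precision of the attachment and childbirth-experience comparisons.

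**Working it through.** **The plan's own figure.** The only design figure is the power for the WHO-5 under Sample size. With 84 completers per arm (168/2) and SD 15.6, SE = 15.6 × √(2/84) = 2.407. Power for a difference of 7 is Φ(7/2.407 − 1.96) = Φ(0.95) = 82.8%; for 8 it is Φ(8/2.407 − 1.96) = Φ(1.36) = 91.4%. These match the stated 82% and 91%, and do not depend on this point.

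**Late end (MAAS).** Randomization is day 0, class 1 is day 14 and three months is 91 days.

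- Earliest permitted due date: 14 + 91 = day 105.
- T2 is day 91, so the margin is 105 − 91 = 14 days, the gap between randomization and class 1.
- A woman at the limit is randomized at 40 − 15 = 25 weeks. She is at 38+0 at T2 and 39+0 at the reminder.

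**Early end (CEQ).** T3 is 26 weeks after randomization.

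- A birth at 40 weeks falls after T3 if randomization was before about 14 weeks (40 − 26). For a birth at 41 or 42 weeks the threshold is about 15 or 16 weeks.
- Time from due date to CEQ: randomized at 14 weeks, 14 + 26 − 40 = 0 weeks; randomized at 25 weeks, 25 + 26 − 40 = 11 weeks.

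**Typical woman.** First consultation at 18 weeks, interview within 2 weeks and consent within 1 more week give randomization at about 18–21 weeks. T2 then falls at 31–34 weeks and T3 at 44–47 weeks, both on the intended side.

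**Chance at the eligibility limit.** Assumption, not in the document: gestation at birth is normal with mean 39.6 and SD 1.8, or mean 39.8 and SD 1.6.

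| Form completed at | Mean 39.6, SD 1.8 | Mean 39.8, SD 1.6 |
|---|---|---|
| 38+0 (T2) | Φ(−0.89) = 19% | Φ(−1.13) = 13% |
| 39+0 (reminder) | Φ(−0.33) = 37% | Φ(−0.50) = 31% |
| 36+0 | Φ(−2.00) = 2% | Φ(−2.38) = 1% |

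**Whole trial.** By simulation with the same birth distributions, births capped at 42 weeks. Gestation at randomization is assumed normal with SD 2–4 weeks, truncated to 8–25 weeks.

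| Quantity | Mean 21 weeks | As women out of 240 |
|---|---|---|
| Delivered by T2 | 0.6–1.6% | about 1–4 |
| Delivered by T2 + 1 week (all reply late) | 2–4% | about 5–10 |
| Undelivered at T3 | 0.1–5% | about 0–12 |

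With mean 18 weeks (no lag between first consultation and randomization), undelivered at T3 rises to about 4–16%, or about 10–38 of 240, and delivered by T2 falls below 1%.

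**The case against.** The case against giving this much weight is strong in several respects.

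- **The eligibility rule does most of the work for the MAAS.** T2 falls at least 2 weeks before the due date for every eligible woman, and the margin grows if a group starts later than the nominal 2 weeks. This stands. The problem is confined to births ahead of the due date and to late replies.
- **The CEQ problem needs early randomization.** It arises below about 14–16 weeks, well under the 18-week average first visit, and Table 1 places an interview, motivational interviewing and a questionnaire in between. The article also does not say that the form closes on the T3 date. This stands, and makes the mean-21 figures more plausible than the mean-18 figures.
- **Form-release rules may sit in an unseen document.** This stands in part. How off-side forms are handled may well be specified elsewhere. The assessment times and the eligibility limit, however, are stated in the article, and they are what permit the overlap.

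A reader might infer that the arms are compared with material bias, because mindfulness training could shift gestational age at birth and so change who has a valid form. The documents do not support that. The Background reports only an indirect effect on gestational age, in a trial of a different adapted programme. Both arms share one clock, so gestation at T2 and recall time at T3 are balanced in expectation, apart from any effect on birth timing. Such an effect would act on only the few women close to the threshold.

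**Conclusion.** The point holds as a scheduling weakness of minor severity. The stated dates allow a MAAS after delivery and a CEQ before it, and they spread the time from due date to CEQ over about 0 to 11 weeks. That much is calendar arithmetic and needs no assumption beyond a 40-week due date.

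How often it happens cannot be established from the document, and the trial-wide percentages rest on assumed distributions. The 13–19% at T2 (31–37% at the reminder) should not be read as a rate for the trial: it describes only a woman exactly at the 25-week limit.

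Nor does the point reach the main result. The WHO-5 analysis, the secondary outcomes and the power do not depend on which side of birth these two forms fall. The main harm is some invalid or missing scores and avoidable noise in the exploratory fourth aim.

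**What to change.** **For women not yet assessed, in both arms alike:**

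1. Send the MAAS at T2 or at 36 weeks by the baseline due date, whichever is earlier. For a woman at the limit this is 36 − 25 = 11 weeks after randomization, still after class 9 at 2 + 8 = 10 weeks. Only women randomized after 36 − 13 = 23 weeks are affected, by at most 2 weeks.
2. Send the CEQ at a fixed interval after the actual birth, for example 6–8 weeks, instead of at T3.

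**For all women, including those already assessed:**

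3. Count only MAAS forms dated before the recorded birth and CEQ forms dated after it, and report how many are set aside in each arm.
4. Include time since birth in the CEQ model. Because birth timing follows randomization, show the result without this term as well.

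**Cost.** A short amendment and a changed sending rule in REDCap. The due date and time of delivery are already collected (Participant characteristics). Recruitment began in March 2022, so each outcome would carry two schedules, the same in both arms. Releasing the CEQ after birth needs timely access to birth dates, which the article does not describe. If that is not feasible, steps 3 and 4 alone need only data already planned. All other questionnaires keep their times.

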### Sample size

The primary outcome is change in mental well-being (WHO-5) from baseline to post-intervention. The aim is to include 240 psychosocially vulnerable pregnant women in the period from March 2022 and until the desired number has been reached. About 750 women are referred to the obstetric ambulatory clinic every year and the time span is therefore considered realistic. Out of 240 pregnant women, 168 (70%) is expected to complete the study based on the dropout rate in the feasibility trial [41]. With this sample size, a standard deviation of 15.6 (data from the feasibility trial) and a two-sided alpha of 5%, the study has 82% power to detect a difference of 7 on the WHO-5 between the two study groups, and 91% power to detect a difference of 8 on the WHO-5.

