### Randomization

The study will use the REDCap randomization module hosted by Aarhus University for the randomization procedure. To secure concealment, a data manager from Aarhus University, not otherwise involved in the study, programed the randomization algorithm. Enrollment and randomization is conducted by the responsible researcher, and takes place after the statement of consent has been signed and the first questionnaire has been filled in. Participants are randomized in a 1:1 ratio. Inclusion and thus randomization will take place consecutively.

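### The model for change in antenatal attachment leaves out baseline attachment, which costs precision on an exploratory outcome

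*Protocol article*

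**What the plan says.** In the protocol article, the Statistical analysis plan section fixes the attachment analysis in one sentence. The outcome is a change score: "The change from baseline to three months after randomization in maternal antenatal attachment will be analyzed". The terms of the model come next: "in a model with the systematic effect of intervention, baseline mental wellbeing, perceived stress, age, number of children and random effect of", where the random effect is that of the class group to which a woman is assigned. The list is explicit. It contains the baseline of another scale (wellbeing) but not the baseline of the scale being analysed, and no other section adds it.

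Table 2 in the Outcomes section shows the "Maternal Antenatal Attachment Scale" completed at T0 and T2, and places it under "Exploratory outcome measures". The Randomization section has the first questionnaire filled in before allocation, so T0 MAAS is a legitimate pre-randomisation covariate. The same section says "Participants are randomized in a 1:1 ratio". In Study aims, attachment belongs to the fourth aim, which is worded as exploration.

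**The concern.** A change score subtracts the baseline with a coefficient of exactly one. If the regression of the T2 score on the T0 score has a slope below one, this subtracts too much. An arm that happens to start higher will then tend to show less change, whatever the intervention does. Putting baseline MAAS in the model lets the data set the coefficient and removes that noise. The other listed covariates can do this only as far as they predict baseline MAAS.

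At stake is the width of the confidence interval for the attachment effect. The outcome is exploratory, but maternal bonding is named in the trial title, so the estimate will be read. The data needed to sharpen it are already being collected.

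**Working it through.** **Inputs from the documents.** 240 women randomised 1:1; "Out of 240 pregnant women, 168 (70%) is expected to complete the study", so 84 per arm; for WHO-5, "a standard deviation of 15.6 (data from the feasibility trial) and a two-sided alpha of 5"%.

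**Assumed, because the documents do not give them.** Equal MAAS SDs at T0 and T2; a T0–T2 correlation rho between 0.5 and 0.9; 84 per arm with a T2 MAAS score (the 70% refers to completing the whole study).

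**The plan's own figure.** It concerns WHO-5, not MAAS: "the study has 82% power to detect a difference of 7 on the WHO-5", and 91% for a difference of 8.
- Standard error = 15.6 × √(2/84) = 2.41.
- Difference of 7: 7/2.41 = 2.91; power = Φ(2.91 − 1.96) = 82.8%.
- Difference of 8: 8/2.41 = 3.32; power = Φ(3.32 − 1.96) = 91.4%.

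With the noncentral t distribution the values are 82.4% and 91.1%. The stated power reproduces. No figure is stated for attachment.

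**Precision of the attachment effect, no other covariates.** In units of SD²:
- change score: 2(1 − rho)
- baseline-adjusted: 1 − rho²
- ratio: 2(1 − rho)/(1 − rho²) = 2/(1 + rho)

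| rho | Variance ratio | 168 completers worth | Power of planned model if adjusted model has 80% |
|---|---|---|---|
| 0.5 | 1.33 | 126 | 68% |
| 0.7 | 1.18 | 143 | 73% |
| 0.8 | 1.11 | 151 | 76% |
| 0.9 | 1.05 | 160 | 78% |

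If the SDs differ (s0 at T0, s1 at T2), the excess variance is s0² + s1² − 2·rho·s0·s1 − s1²(1 − rho²) = (s0 − rho·s1)². This is never negative. It is zero only when the slope of T2 on T0, rho·s1/s0, equals one.

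**With planned covariates in the model.** The simulation used 84 per arm and 3,000 runs per setting, with wellbeing and stress in both models (correlated −0.6 with each other). Wellbeing was correlated c with baseline MAAS, and stress −0.6c. Age, number of children and the group effect were not simulated.

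| rho | c = 0 | c = 0.3 | c = 0.5 |
|---|---|---|---|
| 0.5 | 1.35 | 1.26 | 1.25 |
| 0.7 | 1.17 | 1.15 | 1.10 |
| 0.8 | 1.11 | 1.09 | 1.07 |

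A closed form for this set-up is 1 + (1 − rho)(1 − c²)/(1 + rho). At c = 0.5 it gives:
- rho 0.5: 1 + 0.5 × 0.75/1.5 = 1.25
- rho 0.7: 1 + 0.3 × 0.75/1.7 = 1.13
- rho 0.8: 1 + 0.2 × 0.75/1.8 = 1.08

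The simulated values agree within simulation error. The listed covariates recover part of the loss, not all of it.

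**Where the loss comes from.** Per unit of chance baseline difference between arms, the change-score estimate shifts by −(1 − rho). The simulated slope at rho 0.5 ran from −0.52 (c = 0) to −0.36 (c = 0.5), and at rho 0.8 from −0.20 to −0.16. It was about zero once baseline MAAS was included. The mean error over randomisations was about zero for both models.

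**One quantity, not two.** At rho 0.5 and 84 per arm:
- one-SE baseline difference: √(2/84) = 0.154 SD
- resulting shift: 0.5 × 0.154 = 0.077 SD; squared, 0.0060
- extra variance of the change score: (2/84) × (1.00 − 0.75) = 0.0060

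The shift from chance imbalance is the extra variance seen in a single sample.

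**The case against.** The strongest reply is that the planned analysis is valid. Baseline is measured before allocation, so regression to the mean acts equally on both arms in expectation and the difference in mean change is unbiased. A reader might infer from the missing baseline term that the attachment effect is systematically biased; neither the documents nor the calculation supports that. A reader might also count the sensitivity to chance imbalance as a second harm on top of the lost precision. It is the same quantity, and the change-score standard error already carries it, so the confidence interval covers it. Both parts of this reply stand.

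The change score also matches the primary analysis, whose effect is likewise a difference in change from baseline. That explains the choice of scale but not the omission: with the baseline in the model, the effect on change is the same number as the effect on the T2 score. The covariate list may be shared with childbirth experience, which has no baseline and is to be analysed by equivalent models. That may explain the list but does not justify it for MAAS.

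The size is uncertain. The 33% and 18% figures belong to a model without the planned covariates, and if rho is 0.8 or 0.9 the loss is small in any case. The documents also give no basis for calling baseline MAAS the strongest predictor of the outcome. These limits stand and set the weight of the point. The omission itself remains, because the model is written out and not left open.

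**Conclusion.** The point holds as a loss of efficiency on an exploratory outcome. The planned attachment model omits a baseline value that the trial collects, and its estimate is less precise for any rho below 1 if the SDs at T0 and T2 are equal. Before other covariates the variance inflation is about 33%, 18%, 11% and 5% at rho 0.5, 0.7, 0.8 and 0.9. With wellbeing and stress in the model, and wellbeing correlated 0.5 with baseline MAAS, it is about 25%, 10% and 7% (simulated) at rho 0.5, 0.7 and 0.8. All of these rest on an assumed rho and on equal SDs.

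The point does not reach the WHO-5 analysis, the sample size or the trial's main conclusion. It does not show bias on average, and it does not make the planned analysis invalid. It is an improvement worth making because it is nearly free.

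**What to change.** Add baseline MAAS to the covariates of the attachment model and keep the rest of the list. If the two subscales are analysed, adjust each for its own baseline. The outcome can still be reported as change. Childbirth experience has no baseline measure, so its model stays as it is.

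The cost is one degree of freedom and no new data. Because recruitment began in March 2022 and allocation is not blinded, the change should be made as a dated amendment before outcome data are examined, so that the covariate cannot appear to have been chosen after seeing results.

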Engaging in MBSR is time consuming and requires both great motivation and commitment from the participant. Motivation for change is often high during pregnancy, but the availability of resources may nevertheless be lower in psychosocially vulnerable groups and increase the risk for premature dropout from the intervention. Motivational interviewing (MI) is an evidence-based psychotherapeutic approach that focuses on engaging, encouraging and facilitating intrinsic motivation within the individual to promote behavior change [39]. One study that applied MI in connection with a MBI with the purpose of increasing adherence and reducing dropout reported a significant impact on intervention adherence and dropout rates when compared to a group not undergoing MI [40]. MI will therefore be included in the present study with the aim of increasing adherence and reducing dropout.

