### Design

This protocol adheres to the guidance of the Standard Protocol Items: Recommendations for Interventional Trials (SPIRIT) statement for reporting randomized clinical trials [42]. The design is a single-center, parallel group, randomized controlled trial comparing prenatal MBSR as add on to usual care (UC) with usual care alone. Participants are randomized in a 1:1 ratio to an intervention group or a waitlist control group receiving care as usual. Participants in the waitlist control group are offered participation in an equivalent MBSR program for mother and baby after the follow-up period. An outline of the study timeline is shown in Table 1.

**Table 1 Tab1:** Participant timeline

Timeline	Event
First consultation	Interest in study participation and preliminary eligibility is established at first consultation at the obstetric outpatient clinic (around 18 weeks gestation), and written information is emailed to possible participants.
− 2 weeks	Interview to determine eligibility and participation within two weeks from first consultation.
− 3 weeks	Motivational interviewing (MI)
	Baseline questionnaire
0	Randomization
+ 2 weeks	Start of the intervention (9 weeks)
T1 (1½ months)	1½ months post-randomization: second and intermediate assessment
T2 (3 months)	3 months post-randomization: Third assessment
T3 (6 months)	6 months post-randomization: Fourth assessment
T4 (9 months)	9 months post-randomization: Fifth and final assessment

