### Intervention: the prenatal MBSR program

The prenatal MBSR program is an adaptation of MBSR in order to fit into a clinical context. Importantly, the essential “warp” elements characterizing MBSR were maintained [43]. The adaptation process is described in detail in [name] et al. [41]. In brief, the prenatal MBSR program include nine weekly two-hour classes with a maximum of 15 participants per group. The program is delivered in a combination between physical attendance (class 1, 4 and 9) and live-online teaching. The intention of combining physical attendance with live-online teaching is to reduce travelling and ensure attendance while still providing a good starting point for establishing a learning environment and a sense of community in the group. Pregnancy and motherhood are a natural focus throughout the program, e.g. sitting meditations include periods sitting with one hand on the pregnant belly and the other hand on the heart. Yoga programs suitable for pregnancy was developed. The recommended time for daily mindfulness training between classes is 15 min a day with options for longer practice. This in order to make the course requirements manageable considering the psychosocial vulnerabilities of the women. Participants receive an email after each class summarizing key points from the training and instructions for home practice. Audio recordings with guided meditations and videos with the yoga programs for pregnancy are provided for home practice. Participants are asked to register the time they spent on formal mindfulness practice between classes. The data will be collected after the final class. Participation is registered for each class and participants are encouraged to notify the teacher in case of non-attendance. Participants will be contacted by phone in cases of absence from two successive classes or in cases where the teacher is not notified about non-attendance.

A certified MBSR teacher with a professional background in psychiatry (last author, [name]) teach the prenatal MBSR program. Three midwifes employed at the obstetric ambulatory clinic, who are training to become MBSR teachers, co-teach the prenatal MBSR program. Only one midwife at a time is a co-teacher for a group.

An online booster session is offered three months after finalizing the 9-week program where the new mothers are invited to bring their babies and thus making it an opportunity to practice being mindful with their baby.

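### The supplementary per-protocol contrast of high attenders with the whole waitlist arm can mix treatment effect with selection on attendance; a complier-average estimate should carry the causal claim

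*Protocol article*

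**What the plan says.** The Statistical analysis plan section of the protocol article makes intention-to-treat the basis of the primary analysis: "Analyses on the primary outcome will be conducted on the intent-to-treat population meaning all randomized participants with completed baseline assessments". It defines adherence by a threshold: "Compliance is considered as participation in five or more of intervention-scheduled classes". It then adds a supplementary analysis: "A per-protocol analysis of the primary outcome will be performed with three intervention levels", namely "1) attending five or more of intervention-scheduled sessions, (2) attending less than five of intervention scheduled sessions and (3) waitlist control group".

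The primary effect is the between-arm difference in change since baseline at nine months. It comes from a repeated-measures model with baseline age, perceived stress and psychotropic drug use as covariates and random effects for person and scheduled group. No further method is named for the attendance-based comparison.

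Three other statements matter here. The Intervention section says that "the prenatal MBSR program include nine weekly two-hour classes" and that "Participation is registered for each class". The Design section says: "Participants in the waitlist control group are offered participation in an equivalent MBSR program for mother and baby after the follow-up period".

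**The concern.** Whether a woman reaches five classes is known only after randomization and only in the MBSR arm. The first level contains women who reached the threshold. The waitlist arm contains both those who would have reached it and those who would not. If these two kinds of women would change differently without the program, the contrast carries that difference as well as any treatment effect.

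The article gives reason to expect that attendance is not random. The section on study and intervention adherence ties it to motivation and to physical and mental demands, and the Background says that "the availability of resources may nevertheless be lower in psychosocially vulnerable groups and increase the risk for premature dropout". Motivation is not among the model covariates. At stake is a figure that stands beside the intention-to-treat result and could be read as the effect of full participation.

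**Working it through.** **The plan's own figure.** Sample size section: 240 randomized, 70% completing, so 168, or 84 per arm at 1:1; SD 15.6; two-sided alpha 5%. The normal approximation gives power of 82.8% for a difference of 7 and 91.4% for 8, against the stated 82% and 91%. The stated power reproduces, and this point does not touch it. The SD serves below only as a unit of scale.

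**Bias of the first level against waitlist.** Let π be the share who would attend five or more classes. Let g be the covariate-adjusted difference in change from baseline, without MBSR, between women who would and would not attend. Let τ₁ be the effect in attenders and τ₀ the effect in women below five classes.

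- Level 1 minus waitlist = τ₁ + (1 − π)·g
- Level 2 minus waitlist = τ₀ − π·g
- Intention-to-treat difference = π·τ₁ + (1 − π)·τ₀

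The article gives neither π nor g, so both are assumed. Values of (1 − π)·g in WHO-5 points:

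| π | g = 0.2 SD (3.12) | g = 0.5 SD (7.8) |
|---|---|---|
| 0.6 | 1.25 | 3.12 |
| 0.7 | 0.94 | 2.34 |
| 0.8 | 0.62 | 1.56 |
| 0.9 | 0.31 | 0.78 |

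If the two kinds of women differ equally at baseline and at nine months, g = 0 and the bias is 0. If g is negative, the bias is negative.

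**Complier-average estimate.** The waitlist arm is not offered the program until after follow-up, so non-adherence is taken as one-sided. The estimate is then the intention-to-treat difference divided by π. If τ₀ = 0 it equals τ₁, whatever g is. Its standard error is about 15.6·√(2/84)/π = 2.41/π, or 3.44 at π = 0.7.

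**Simulation.** 84 per arm, 4,000 runs, π = 0.7, g = 7.8, simple mean comparisons of an outcome with SD 15.6:

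| τ₁ | τ₀ | Level 1 vs waitlist | Level 2 vs waitlist | Complier-average |
|---|---|---|---|---|
| 0 | 0 | 2.35 | −5.42 | −0.03 |
| 7 | 0 | 9.32 | −5.44 | 6.95 |
| 7 | 3.5 | 9.30 | −1.92 | 8.45 |

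In the first row, level 1 against waitlist is significant at 5% in 14% of trials.

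**Limit of the complier estimate.** If τ₀ = f·τ₁, it is biased by f·τ₁·(1 − π)/π. With f = 0.5, τ₁ = 7 and π = 0.7 this is 0.5 × 7 × 0.3/0.7 = 1.5, so about 8.5 against a true 7. That is less than the per-protocol bias of 2.34 at g = 7.8, but more than the 0.94 at g = 3.12.

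**The case against.** The strongest case against is that the plan already limits the damage. Intention-to-treat is primary. The effect is a change from baseline with covariates, so a stable difference in level cancels. Low attenders are not dropped but shown as their own level, where selection may become visible (−5.42 in the null simulation). Eligibility excludes women unavailable for two or more classes, and motivational interviewing precedes randomization, so non-attendance may be modest. The complier estimate needs its own assumption, and the article makes that assumption doubtful: the adherence section implies that women who drop out may still get part of the benefit, and MBSR participants also receive emails, recordings, follow-up calls and the offer of individual sessions.

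Most of this stands. It limits the size of the problem and rules out presenting the complier estimate as assumption-free. It does not make the level 1 contrast a randomized one. Baseline adjustment cannot be relied on to remove selection on motivation or on events during follow-up. A visible deficit in level 2 does not correct level 1, nor can it be told apart from a real effect in low attenders.

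A reader might infer three stronger things that the article does not support:

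- That the analysis will show a benefit even if the program does nothing. This needs g > 0, and the article does not give the sign of g. Regression to the mean among women starting lower could push the other way.
- That the article says less-resourced women within the trial attend less. The Background sentence describes vulnerable groups as a whole, which is the trial population.
- That the plan gives up the randomized comparison. It does so only in this supplementary analysis.

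**Conclusion.** The point holds for the supplementary analysis only. As planned, the contrast of women attending five or more classes with the whole waitlist arm can mix treatment effect with selection, and the article names nothing that separates the two. Over attendance of 60–90% and an adjusted gap in change of 0.2–0.5 SD, the shift is about 0.3 to 3.1 WHO-5 points, against a planning difference of 7. These shares and gaps are assumptions, taken here to favour attenders. The true shift could be zero or negative. The primary intention-to-treat estimate and the stated power are unaffected. A complier-average estimate is feasible with data already collected and removes this selection if fewer than five classes have no effect. Because that condition is doubtful here, the estimate needs sensitivity versions.

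**What to change.** Add to the analysis plan a complier-average causal effect on WHO-5 change at nine months, as the causal estimate of participation. Use randomization as the instrument for attending five or more classes, by two-stage least squares or an equivalent likelihood model, with the same covariates and allowance for scheduled group. State the assumption that allocation has no effect in women attending fewer than five classes. Add two sensitivity versions: any attendance as the exposure, and number of classes attended as the exposure. The latter drops the threshold but gives a weighted average effect per class. Keep the three attendance levels as a table labelled descriptive and non-causal.

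The cost is wording, one further model and its two variants; no new data are needed because attendance is recorded per class. The downsides are a standard error roughly divided by the attendance share (2.41 becomes about 3.4 at 70%), reliance on the no-effect assumption, and a stated missing-data assumption for the expected 30% dropout.
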